##### Attention-control group

Participants in the attention-control group will receive standard sleep literature by a control group peer health educator, who will provide general information about OSA and access to available sleep services through pamphlets. Similar to procedures that will be followed for participants in the intervention arm, health educators will advise all participants at risk for OSA to seek OSA home evaluation by contacting the research program coordinator to schedule a home visit and move through the continuum of care described above.

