### Study rationale

The primary aim of this trial is to ascertain (1) the effectiveness of tailored, peer-based sleep health education and social support in increasing adherence rates to recommended OSA evaluation (adherence to sleep home-based study is categorized as ‘yes’ or ‘no’ depending on whether the individual participated in a sleep home-based study and adherence to sleep clinic assessment is categorized as ‘yes’ or ‘no’ depending on whether the individual had a laboratory-based sleep clinic assessment) and treatment among blacks at risk for OSA (adherence will be defined as whether the participant wore their CPAP device > 4 hours a night for 70% of the nights); and (2) the rate of OSA among black men and women at the community level using home-based sleep recordings. Early identification of OSA via home-based studies in this high-risk population could potentially lead to early OSA treatment and prevention and may reduce subsequent health consequences such as CVD and premature death. Our study can be used as a national model for how to increase racial/ethnic minority engagement in the healthcare system through culturally responsive strategies that bridge underserved communities. Thus, our proposal to screen blacks in community settings, such as barbershops, beauty salons, and places of worship, will maximize the likelihood of recruiting and enrolling a representative sample of blacks.

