#### Randomization to intervention or attention-control groups: allocation and blinding

Participants will be randomly assigned to either the intervention arm (partnered with a peer health educator who received the culturally and linguistically tailored sleep health education and was trained for 8 weeks) or the attention-control group (the comparative group where participants are partnered with a peer health educator who did not receive tailored sleep health education but only standard health training for a 1 hour session). The unit of randomization is the participant and thus the unit of analysis will be at the participant level. All study staff except for the data manager and project coordinator will be blinded to participant assignment. The data manager generates the randomization sequence for each eligible participant and the study coordinator randomly assigns peer health educators to participants assigned to treatment and attention-control groups. We will un-blind participant assignment only in cases where the participant’s health is at risk due to CPAP usage (Fig. 3).

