#### Sample size and power analysis

We plan to screen approximately 1250 blacks in the community. Assuming 39% of blacks are at risk for OSA, we propose to enroll 398 men and women (199 per study arm). With a 35% attrition rate, 258 will have provided adherence data during 6-month follow-up assessment. Based on the pilot data, we expect that 41% in the intervention arm (*n* = 82) and 26% in the attention-control arm (*n* = 52) will have completed all aspects of the trial, including site interview, home evaluation, and follow-up assessment (Fig. 2).

The primary study outcome is receipt of home OSA evaluation after tailored peer-based sleep health education. Data obtained from a sample of blacks provided a current estimate of the likely OSA evaluation rate we expect in the partner community. Analysis showed that 41% of participants adhered to recommended OSA evaluation after intervention exposure, whereas 26% of participants in a control group agreed to undergo evaluation. These preliminary findings represent the likely adherence rates expected in our proposed study.

We propose to achieve an evaluation rate in our intervention arm of 41% based our pilot study mentioned above. This would represent a 63% greater adherence rate compared with controls, which potentially would have a significant public health impact. Assuming a 15% increase in the likelihood of undergoing home-based OSA evaluation, a standard error of 0.09% and a sample size of 398, the study will be adequately powered (> 85%) to detect a significant increase in adherence. Specifically, an observed difference of 15% would be reported with a 95% CI 7–24%. A two-tailed test, with 80% power and α = 0.035 comparing adherence rates of 26% with 41% requires 199 participants per group. Of note, our sample size estimate adjusted for potential intra-cluster coefficient that may be observed in both the treatment and control arms, which according to our initial pilot was 0.014. The resulting effective sample size (*ESS = [M x K/DE]*) after adjustment for design effect (*DE*)… [*DE = 1 + (n-1)ρ*] was *n* = 398 (199 participants per arm) [97, 98]. The study is also powered to assess differences in adherence rates to CPAP treatment between the two arms considering the likely attrition rate of 35% during follow-up assessment.

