### Limitations and challenges

Our study has several potential design and analytical limitations and challenges. A primary design challenge is to uphold blinding of participant assignment among key personnel. Only the project coordinator and data manager are aware of participant assignment to either the treatment or intervention group. To safeguard against unblinding, we have set up a very strict policy as to who can have access to data (blinded personnel do not have access to data), how project details are communicated in the team where all data are de-identified, and periodic checks to ensure integrity of data will be made by the data manager, who does not attend research project team meetings nor receives project-related email correspondence. A primary analytical challenge is our use of GEE, which is ideal to test our hypotheses and deal with unmeasured dependencies between outcomes. However, GEE requires a large sample size, which the study is powered for, but if we do not meet adequate sample size our power to make meaningful inferences using GEE will be compromised. As an alternative analytical plan, we would use analysis of covariance, which will improve our ability to detect significant effects on our primary and secondary outcomes using a smaller sample size.

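### The home sleep study that forms the primary outcome may be booked by a coordinator who knows the arm; the article should say who books it and give the task to blinded staff

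*Protocol article*

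**What the plan says.** - **Outcome.** Sample size and power analysis: "The primary study outcome is receipt of home OSA evaluation after tailored peer-based sleep health education". The Study rationale scores it yes or no, "depending on whether the individual participated in a sleep home-based study". Under the primary trial outcome heading in Phase III, research staff and a technician carry out the home study.
- **Route.** The Attention-control group section says that participants are advised to obtain the evaluation "by contacting the research program coordinator to schedule a home visit". The sentence begins "Similar to procedures that will be followed for participants in the intervention arm, health educators will advise all participants at risk for OSA", so the stated route is the same in both arms.
- **Who knows the arm.** Section on allocation and blinding: "All study staff except for the data manager and project coordinator will be blinded to participant assignment". Limitations and challenges: "Only the project coordinator and data manager are aware of participant assignment".
- **Who pairs educators with participants.** The allocation section adds that "the study coordinator randomly assigns peer health educators to participants assigned to treatment and attention-control groups".

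**The concern.** The outcome is not something that happens to the participant independently of the trial. It is a visit that the study team has to book and carry out. If the person who books it knows the arm, quicker replies, more flexible slots or more rebooking after a missed visit in one arm would change the number of completed home studies. Blinded ascertainment at 6 and 12 months would not help, because it would record correctly an event whose occurrence had already been influenced. Because the article presents this booking step as common to both arms, uneven handling of it would be bias and not part of the tailored education being tested.

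**Working it through.** **Tracing the roles**

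1. The event is a completed home study (Study rationale; Sample size and power analysis).
2. The stated route in both arms is participant contact with the *research program coordinator* (Attention-control group). The article describes no other route, though it does not say that none exists.
3. The *project coordinator* and the data manager know the arm; all other study staff are said to be blinded (allocation section; Limitations).
4. The *study coordinator* pairs educators with participants within each arm, and so must know the arm. Under step 3 that is consistent only if the study coordinator is the project coordinator. This indicates that the article uses its coordinator titles loosely.
5. The project coordinator already deals with participants: as a retention contact (Data collection and management), for close-out or onward steps after the home study (Phase III) and at debriefing (Phase V).
6. Steps 4 and 5 make it natural to read the research program coordinator as the same role. No sentence confirms it. If that person is someone else, step 3 makes the booker blinded.
7. The safeguards under Limitations cover access to data, de-identified communication and the data manager's separation from meetings and email. None concerns booking.

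**What a given shift would do (shifts assumed, not taken from the documents)**

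Inputs from Sample size and power analysis: 26% versus 41%, 199 per arm, two-sided α = 0.035 (critical value 2.108). Clustering is ignored.

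The target difference is 0.15 × 199 = 29.9 participants. The article's counts give 82 − 52 = 30; it describes these as completing all aspects of the trial, but uses the same rates for the primary outcome.

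For a pooled z-test with rates p1 and p2 and mean p:
- SE0 = √[2p(1−p)/199]
- SE1 = √{[p1(1−p1) + p2(1−p2)]/199}
- upper-tail rejection probability = Φ[(p1 − p2 − 2.108·SE0)/SE1], plus the lower tail.

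The plan's own figure first: with 0.41 versus 0.26, SE0 = 0.0473 and SE1 = 0.0467, so Φ(1.075) = 85.9%. This agrees with the stated power above 85%.

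Next, no true effect (26% in both arms), with booking adding a fixed amount in the intervention arm. For 5 points, 0.31 versus 0.26 gives SE0 = 0.0453 and SE1 = 0.0452, and Φ[(0.05 − 0.0954)/0.0452] = Φ(−1.005) = 15.7%. The lower tail adds 0.1%, giving 15.8%.

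| Assumed shift | Participants of 199 | Share of 15-point target | Rejection rate, no true effect |
|---|---|---|---|
| 0 points | 0 | 0% | 3.5% |
| 2 points | 4.0 | 13% | 5.4% |
| 5 points | 10.0 | 33% | 15.8% |
| 10 points | 19.9 | 67% | 51.9% |

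A shift can also go the other way. If the true rates are 41% and 26% and booking takes 5 points from the intervention arm, the comparison becomes 36% versus 26%. Those are the rates in the last row, so power falls from 85.9% to 51.9%.

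**The case against.** The strongest objection is that the decisive link is missing from the text. The booker carries a title that differs from that of the unblinded role, and the article says that all other staff are blinded. A separate program coordinator would therefore be blinded and the concern would largely fall away. This stands, and it is why the point is conditional and why the first request is for clarification.

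A reader might go further and infer that the home study happens only when an unblinded coordinator allows it. The documents do not support that. The participant makes the contact and must accept the visit, the stated route is the same in both arms, the staff who carry out the study are described as blinded, and nothing gives the coordinator discretion to refuse or delay a request. Nor is the pairing of educators a source of bias in itself: it is described as random, and shows only that the person doing it knows the arm.

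It can also be said that booking scripts belong in a manual of procedures and that an article may omit them. That is fair for the scripts. The point here rests on two things that the article does state, the booking route and the list of unblinded roles, and on how they combine.

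Finally, more home studies in the intervention arm are what the trial hopes to see, since its educators encourage evaluation and ask about the home visit. That is correct. It is also the reason to be able to tell a difference in requests from a difference in how requests were met.

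**Conclusion.** The point holds as a conditional risk of bias in the primary outcome. It rests on one inference, that the research program coordinator is the unblinded project coordinator. The loose use of titles favours that reading but does not prove it. The documents do not show that any bias occurred, and its size and direction are unknown. The shifts of 2, 5 and 10 points are illustrations; they show only that about ten participants handled differently in one arm would matter against a target of about thirty. The change is worth making because no stated safeguard covers booking and the remedy is cheap.

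**What to change.** 1. State whether project, study and research program coordinator are one role and, if not, which of them know allocation.
2. Have home-visit requests from both arms booked by existing staff who are blinded under the allocation section, with the same offer and rebooking procedure in each arm. State that the unblinded coordinator does not book home visits.
3. Log the date of each request and of each completed home study, and report both by arm, so that differences in requests can be separated from differences in fulfilment. Completion after a request also depends on the participant's own follow-through, so noting each offer and rebooking attempt would make the log more useful.

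The cost is one reassigned task and a small log. Recruitment was ongoing at publication, so the change could apply to later participants, with the date of the switch recorded. The protection is partial, because callers may reveal their arm; the common procedure and the log still limit discretion and make any imbalance visible.

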### Phase III: OSA assessment and diagnosis – home study and sleep clinic assessments and treatment customization

#### Primary trial outcome: sleep home study

The research staff will conduct an 8-day home study to collect sleep data via actigraphy (ActiGraph WGT3X-BT monitor) and a daily sleep diary, as well as environmental influences of sleep, such as noise and temperature, two factors that may confound sleep duration and quality. On day 1 of home sleep, a study technician will visit the participant’s home to place the ActiGraph watch on the participant’s wrist as well as connect a sound device and thermometer to capture the participant’s physical sleep environment. During the visit at the participant’s home, staff will demonstrate how the WatchPAT™ home sleep test device is used, worn on the wrist and fingertip on the last night of a 7-day sleep diary. On the seventh day of the home evaluation, the study’s technician will re-visit the participant’s home to set-up a device, the WatchPAT™ portable sleep test device to determine the severity of OSA risk. The WatchPAT™ is an in-home device utilized for OSA evaluation cleared by the Food and Drug Administration and approved by the Center for Medicare & Medicaid Services [93, 94]. It measures blood oxygen saturation, pulse rate, airflow, respiratory effort (a combined signal using pressure transducer sensing forehead venous pressure, venous volume by photoplethysmography), and snoring levels. Automated analysis of physiologic data yields OSA indices that reflect OSA risk, which is verified by a trained human scorer to ensure accuracy of signal interpretation. The device integrates physiologic, clinical, and anthropomorphic data to determine the presence and severity of OSA. Correlation between the WatchPAT 200 and PSG recordings was 0.96 using AHI with a 4% desaturation. Diagnostic sensitivity and specificity of in-home WatchPAT using AHI ≥ 15 (in the absence of OSA symptoms) are 0.85 and 0.91, respectively [93]. Based on Medicare guidelines [95], those with an AHI ≥ 10 will be referred for treatment (American Academy of Sleep Medicine guidelines) [96]. We chose this criterion to ensure that we reduce the rate of false negative results. In the 7-day sleep diary, participants will indicate (1) nap time and duration, (2) medications/drugs promoting night-time sleep or daytime alertness (e.g., caffeine), (3) time to bed, (4) time of lights off, (5) final time of awakening, (6) final time of arising, and estimated (7) sleep latency, (8) sleep duration, (9) wake after sleep onset, (10) sleep quality, and (11) daytime sleepiness. On day 8, the study staff will retrieve all devices and data from the sleep diary.

After the home sleep study, the study staff will provide the results to the study physician to determine the risk of sleep apnea from the WatchPAT™ home sleep recorder device. The study physician will discuss the home study results with all participants and will recommend treatment to those meeting OSA diagnostic criteria (AHI > 10). Participants who do not meet OSA diagnostic criteria will be transferred to the project coordinator either for study close-out since they no longer need to continue their participation in the study, for future clinic-based diagnostic assessment, or for treatment customization. Participants who are at risk for OSA will be referred for further diagnostic assessment and treatment to a sleep clinic accredited by the American Academy of Sleep Medicine. Expenses incurred from laboratory and CPAP procedures recommended by sleep clinicians in our catchment area will be billed directly to the participant’s insurance. In the rare instance that a participant might fail to obtain insurance, the study project will absorb some medical costs and a CPAP device will be dispensed as an in-kind contribution.

#### Secondary trial outcome: sleep clinic assessment, diagnosis, and treatment customization

Participants who have a high AHI (≥ 10) will be referred for sleep assessment to determine OSA diagnosis and appropriate treatment. Peer health educators will support participants as they navigate this phase of their care by helping them with scheduling appointments and occasionally accompanying them to appointments if requested by the participant, as well as providing general information about the sleep assessment. The purpose of this level of social support is to demystify the OSA assessment (which includes self-report screener, home study, and clinic study using polysomnography) experience, which can be daunting and might deter participants from undergoing the sleep assessment. In our previous research, we found that blacks were less likely to adhere to recommended OSA treatment and therefore the use of peer health educators is a practical way of increasing CPAP adherence.

### Phase IV: third trial outcome – continuous positive airway pressure (CPAP) adherence

Participants who are diagnosed with OSA and are prescribed CPAP will be provided a CPAP machine at their residence by a technician from the CPAP company. The technician will provide standard initialization of the CPAP machine and a to-do kit that provides general use and care guidelines for the machine. The participant’s assigned peer health educator will resume peer education sessions with the aim of motivating the participant to adhere to the recommended use of the CPAP machine. This is a critical period in OSA treatment, as a significant number of patients do not adhere to recommended treatment. Therefore, the role of the peer health educators is very important because they can provide tailored sleep health education on the importance of adhering to CPAP, address barriers preventing the participant from complying with treatment, and help to motivate participants to adhere to treatment.

### Phase V: debriefing and exit interviews

#### Exit interviews

At the end of the 12 month enrollment in the study, all participants will be debriefed by the project coordinator. Participants will complete the same baseline questionnaires and additional questionnaires designed to understand why participants adhered to the intervention and how the intervention might be refined to be more effective.

#### Compensation

Participants can receive up to US$ 125 for completing all the study visits, including US$ 5 for the screening visit, US$ 60 for the baseline and home study visit, US$ 30 for the 6-month follow-up visit, and US$ 30 for the 12-month follow-up visit. If participants choose to withdraw from the study before finishing the study*,* they will be paid up to the point of withdrawal.

#### Data safety and monitoring

All participants’ data and patient health information will be confidential and protected during and after the trial. A code will be used to identify study participants, which will not be given to anyone outside of the study staff unless required by law. All paper records are stored in an area with two locked doors and/or drawers. Only the study staff will have access to the locks. All computerized records are password protected available only to the study team. We will use a data monitoring committee independent of the funding source to provide oversight on integrity of the collected data. We will perform yearly audits to ensure that study protocol is followed.

#### Risk/benefit assessment

Sensors used for the sleep study recordings may cause minor skin irritation among people with sensitive skin; this does not usually require medical attention. Such irritation can easily be resolved with over-the-counter ointment that can be obtained at a local drug store. Participants may not directly benefit from being in this study. However, possible future benefits include increased awareness and learning about sleep apnea and receiving treatment for sleep apnea among those with an OSA diagnosis. If participants experience any harm due to participating in the study, we will follow all New York University ethical review board guidelines, which include (1) ensuring medical safety of participants by providing any medical treatment needed; (2) investigating the incident, determining if risk is inherent to study procedures, and submitting an adverse event report to the New York University ethical review board; and (3) making necessary updates to the protocol and notifying currently enrolled participants about the given risk.

#### Ethics and dissemination

The current trial and aforementioned procedures were approved by the New York University School of Medicine Institutional Review Board. Any changes to the protocol will need to be approved by the Institutional Review Board and the enrolled participants and funder will be notified. At the completion of data collection, the principal investigator and data analyst will process and analyze the data. Findings will be disseminated to the communities from which participants were recruited as well as to the funder. The data will be made publicly available 5 years after completion.

